These data will inform the design of a future randomised control trial , investigating the efficacy of an early EMDR R-TEP intervention in reducing psychological morbidity for Covid-19 related critical care survivors.

**Method:** Hospital-based research staff will approach consecutive eligible patients in hospital or within 12-weeks of hospital discharge to discuss the trial and to present the Patient Information Sheet. Consenting patients will complete baseline assessments, before random allocation to treatment or usual care. Patients in the intervention arm will be referred to an NHS psychological therapy service, whose staff are trained and experienced EMDR R-TEP practitioners. The psychological therapy service will arrange for an online, virtual baseline visit. There will be a minimum of 2 and a maximum of 8 sessions depending on patient need, assessed by the treating psychological practitioner, as per the EMDR R-TEP protocol. Each session lasts for 60-90 minutes. When the practitioner assesses that the patient is no longer experiencing disturbing thoughts or memories, the intervention will be complete.

The patient will be asked to repeat the assessments, 6-months following discharge from hospital. In addition, we will complete a post-study, process evaluation, consisting of semi-structured interviews with a representative sample of participants and staff.

**Outcomes:** Primary outcome will be feasibility and tolerability of the intervention. This will be assessed by recruitment rates and adherence to the EMDR R-TEP intervention and follow-up assessments.

Exploratory data of effectiveness will be collected by patient-reported questionnaire. We will assess PTSD symptoms using the PTSD CheckList – Civilian Version (PCL-C). We will assess anxiety and depression using the Hospital Anxiety and Depression Scale (HADS) and EuroQol Five Dimension- Five level scale (EQ5D-5L). The Montreal Cognitive Assessment (MOCA) tests cognitive ability. Patients will be asked to wear an activity monitor for 7-days. The Council of Nutrition Appetite Questionnaire (CNAQ) and Brief Resilience Scale (BRS) will also be completed at baseline and 6-months post-discharge.

The process evaluation will reveal themes that we will use to assess fidelity, quality and implementation.

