To ensure adherence with social distancing guidelines, our expert psychological therapy team have begun to deliver the EMDR therapy via online videoconferencing. This has been shown to be equally as effective as face-to-face sessions and is supported by the NHS technology arm, British Psychological Society and the American Psychiatric Association. The additional advantage is that ICU survivors will be spared a journey to a treatment centre and can undertake the therapy at home or the location of their choosing. Because we think that this is worthy of extra investigation, we aim to determine whether it is feasible to deliver online EMDR therapy to survivors of Covid-19 related critical illness and whether it might help to reduce psychological trauma associated with the illness and treatment.

A total of 26 survivors of intensive care, will be offered the EMDR therapy, in order to see whether they feel it is a good idea and whether they will volunteer to undertake sessions with a highly trained and experienced team of psychological therapists. These patients will be randomly placed into one of two groups.

In the ‘intervention group’, 13 patients will be referred to a local NHS community-based EMDR therapy team, run by expert Clinical Psychologists. They will attend between 2 and 8 online sessions, starting within 12-weeks of hospital discharge. We will ask our patients to complete some survey questionnaires, before and after therapy, to see whether it makes them feel better about their stressful experience. We will also record whether the patients completed the therapy and how they felt it might be improved or made more accessible.

In the ‘control group’, the remaining 13 patients will undertake all of the same questionnaires, but will not receive online EMDR. Patient’s final involvement will be to repeat the questionnaires 6-months after they have been discharged from hospital.

When the trial has been completed, we will ask to interview a number of trial participants and staff involved in the trial. The information that we gain from this study will be used to design a much larger study, which will investigate whether EMDR can be effective for all survivors of intensive care.

1. **Background and rationale**

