**Secondary outcome measures**

All secondary outcome measures will be collected at baseline and 6-months post-hospital discharge

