- Is life-threatening – refers to an event in which the subject was at risk of death at the time of the event; it does not refer to an event which hypothetically might have caused death if it were more severe
- Requires hospitalisation, or prolongation of existing in participants’ hospitalisation
- Results in persistent or significant disability or incapacity

**Suspected Unexpected Serious Adverse Reaction (SUSAR):** any suspected adverse reaction related to the trial procedures that is both unexpected and serious.

1. **Data collection and confidentiality**

Demographic and baseline questionnaire data will be collected following consent. Research nurses at the recruiting site will contact the participants via telephone at 4-months post-hospital discharge (+/- 2-weeks). Participants will be invited to repeat the baseline questionnaires, which will be posted to them with a pre-paid envelope. If participants prefer, the questionnaires can be completed over the telephone. These data will be securely stored as paper case report forms at the recruiting site.

All entries must be clear, legible and concordant with Good Clinical Practice. The local Principle Investigator is responsible for accuracy of data. Participating staff must be listed on the signed delegation log.

Prior to commencing the online conversation the therapy team will reiterate the boundaries of confidentiality and ensure ongoing consent. The participant’s preference of Skype^TM^ or Zoom^TM^ will be used in accordance with NHS Digital guidance. The therapist will not record the videoconference, unless specifically asked to do so by the participant, in which case written consent will need to be attained and the recording will be treated as part of their medical record. As in any other consultation, the therapist will ensure GDPR compliance for data storage and processing according to NHS Digital standards. [74]

The CovEMERALD study team and participating sites will act concordant with the Medical Research Council’s Guidelines for Good Clinical Practice in Clinical Trials and Good Research Practice: Principles and Guidelines.

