1. **What (procedure)**: Twenty-six eligible participants from a UK critical care unit will be recruited for the study. After gaining their consent, a baseline assessment will be carried out through the outcome measures mentioned in point 3 above. Participants will then be referred to the Intensive Psychological Therapies Service in Poole where the online EMDR R-TEP intervention will be arranged. The intervention itself will involve 2-8 one-hour sessions in addition to a follow-up assessment at 6 months post-hospital discharge. A post-hoc process evaluation will be completed via semi-structured interviews with study participants, a representative sample of trial decliners, and clinical staff in order to gain qualitative data regarding the perceived efficacy of the intervention.

EMDR R-TEP is a comprehensive current trauma-focussed protocol for early EMDR intervention. The EMDR R-TEP has an 8-phase approach and usually requires 2-4 sessions, which can optionally be conducted on successive days [87] (Shapiro & Laub, 2014). In its essence, the EMDR R-TEP is an adaptation of EMDR for early intervention, integrating existing wisdom while addressing some additional issues of the trauma. The EMDR R-TEP conceptualises the traumatic event as a fragmented experience which has not yet been consolidated so no single image represents the entire event. The EMDR R-TEP enables the processing of a number of targets, which are aspects or parts of the event in order to facilitate integration and consolidation [84] .

The 8 phases of EMDR R-TEP include:

1. Client history: Obtaining information about the client’s previous pathology, exploring their severity, motivation and strengths as well as administering the IES-R trauma screen.
2. Preparation: using stabilisation exercises (e.g. 4 elements, Safe/Calm Place) followed by bilateral stimulation and scanning whilst the client is describing a traumatic episode.
3. Assessment: The client describes a target, a negative cognition and a positive cognition followed by a measurement of their subjective units of distress (SUD)
4. Desensitisation: doing sets of bilateral stimulation to gradually reduce the client’s subjective units of distress
5. Installation: involves the installation of a positive cognition, with the validity of that cognition being evaluated at regular intervals in-between more periods of bilateral stimulation

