6. Body scan: the client is asked to notice body sensations while bringing the target trauma to mind, with any residual body tension being reprocessed by the clinician
7. Closure: ensures a strong closure to target processing and a return to the stabilisation exercises
8. Re-evaluation: the client’s subjective units of distress and the validity of their positive cognition are re-evaluated followed by a re-administration of the IES-R trauma screen
9. **Who provided**: The intervention will be delivered by experienced clinicians who have been trained in EMDR R-TEP (2-day training workshop) by the treatment developer ([name]) and have completed Part I and Part II of basic EMDR training. These will include a Consultant Clinical Psychologist and Psychological Therapists who have expertise working with clients presenting with complex trauma and enduring mental health difficulties such as PTSD and Personality Disorder.
10. **How**: R-TEP will be delivered online, via Skype or Zoom, on an individual basis for each participant. This will be over the course of 2-8 sessions. Following completion of R-TEP, participants will be contacted through post for their 4-month follow-up in order to complete the repeat outcome measures.
11. **Where**: Once eligible participants have consented to participate in the study, they will be referred to the Intensive Psychological Therapies Service team located at Branksome Clinic in Poole (Dorset). Online EMDR R-TEP sessions (including follow-up) will take place using the participant’s preferred platform of Skype or Zoom, in accordance with NHS Digital guidance. The environment is remote from the scene of the trauma (i.e. hospital) and we are hoping that this would cause less distress to participants while they are engaging in the intervention. In addition, the use of an online platform will enable access to. Abroad population of patients who may be physically unable to travel to a psychological service clinic. Branksome Clinic is a tertiary service for outpatients, who present with complex trauma and enduring mental health difficulties, and is part of the Dorset HealthCare University NHS Foundation Trust. The service consists of a multi-disciplinary team of therapists from a variety of core professional backgrounds such as Clinical Psychology, Nursing and Occupational Therapy. All staff are professionally trained, post qualification, in a minimum of one therapy that is delivered at the service.

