12. **When and how much**: The R-TEP intervention for this study is planned to take between 2-8 weekly sessions per participant. Each session will last 60-90 minutes. At 4-months post-hospital discharge all patients will be contacted via telephone, by NHS research nurses, in order to arrange a repeat of the baseline assessments completed following consent. Patients will be able to complete these assessment questionnaires by post or over the telephone.
13. **Tailoring**: The number of therapy sessions can vary on an individual basis depending on the participant’s severity of the identified trauma and how able they are to address it during treatment. This will be discussed with the treating clinician and mutually agreed prior to establishing the therapeutic framework of the intervention. Another aspect which can be tailored is whether the 3-month follow-up session is completed face-to-face or through telephone depending on the participant’s needs.
14. **Modifications**: None expected
15. **How well (planned)**: All clinicians who will deliver EMDR R-TEP in this study have been trained in the delivery of the intervention and will adhere to a standardised protocol of treatment. The number of therapy sessions can vary depending on each participant and this is an aspect of the study which can be difficult to control or plan in advance. We will be collecting adherence data as our primary outcome. These will inform the design of a future randomised controlled trial.
16. **How well (actual)**: to be reported following trial completion.

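### The single post-baseline outcome assessment is set at 6 months after discharge in the outcome section and schedule, but at 4 months in Section 12 and parts of Appendix 2

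*Protocol*

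**What the plan says.** Six places put the repeat assessment at 6 months after discharge:

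- Abstract, Method: "The patient will be asked to repeat the assessments, 6-months following discharge from hospital".
- Lay summary: participants are to "repeat the questionnaires 6-months after they have been discharged from hospital".
- Section 8.6, secondary outcome measures: "All secondary outcome measures will be collected at baseline and 6-months post-hospital discharge".
- Section 8.6, physical activity: the wristband is worn again at 6 months, which is described as the final assessment.
- Schedule of events (Figure two): the only follow-up column for the outcome measures is 6 months.
- Appendix 2, *What (procedure)*: therapy is given "in addition to a follow-up assessment at 6 months post-hospital discharge".

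Three places put it at 4 months:

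- Section 12, Data collection and confidentiality: "Research nurses at the recruiting site will contact the participants via telephone at 4-months post-hospital discharge (+/- 2-weeks"). The next sentence makes clear that this contact is for repeating the baseline questionnaires.
- Appendix 2, *How*: "participants will be contacted through post for their 4-month follow-up in order to complete the repeat outcome measures".
- Appendix 2, *When and how much*: "At 4-months post-hospital discharge all patients will be contacted via telephone, by NHS research nurses".

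Appendix 2, *Tailoring*, adds a third interval, on "whether the 3-month follow-up session is completed face-to-face or through telephone".

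**The concern.** Section 12 is the operational text. It says who makes contact, when and how, and it gives the only visit window in the protocol; the 6-month date has none. A nurse who follows it would collect the questionnaires well before the time at which the outcome section defines the secondary outcomes.

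Three things are at stake.

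- **Feasibility criterion.** One primary criterion is completion of the outcome measures by at least 75% of participants. Completion has no unique due date, so a questionnaire that is on time under one section is about two months early under another.
- **Use of the results.** Section 9 says the results will be used to power a definitive study. Means, standard deviations and completion rates observed at 4 months need not apply to a 6-month endpoint.
- **Position relative to therapy.** Therapy may start up to 12 weeks after discharge and run to 8 weekly sessions. The earlier date therefore does not guarantee that every intervention participant has finished.

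**Working it through.** No design formula applies, because the disputed figure is a visit time. The check is calendar arithmetic on the protocol's own limits.

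**1. The two dates in weeks.** One month = 365.25 / 12 / 7 = 4.348 weeks.

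- 4 months = 4 × 4.348 = 17.39 weeks. The Section 12 window is 17.39 ± 2 = 15.39 to 19.39 weeks.
- 6 months = 6 × 4.348 = 26.09 weeks.
- Difference = 26.09 − 17.39 = 8.70 weeks.
- If the 6-month date also had a window of ± 2 weeks (an assumption, as none is stated), it would open at week 24.09. That is 24.09 − 19.39 = 4.70 weeks after the other window closes, so no assessment could be on time under both.

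**2. Position relative to therapy.** Inputs: first appointment within 12 weeks of discharge (Section 8.5); 2 to 8 weekly sessions (Appendix 2, *When and how much*). With the first session in week *a*, session *s* falls in week *a* + (*s* − 1). For *a* = 12, the latest permitted start, sessions 4 to 8 fall in weeks 15, 16, 17, 18 and 19.

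- Nominal 4 months (week 17.39): session 6 is done, sessions 7 and 8 are not. A course of 7 or 8 sessions overlaps.
- Window opening (week 15.39): session 4 is done, session 5 is not. A course of 5 or more overlaps.
- Window closing (week 19.39): all 8 are done, by 19.39 − 19 = 0.39 weeks.
- 6 months (week 26.09): the eighth session is 26.09 − 19 = 7.09 weeks in the past.

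For a full course of 8 to be finished, the first session must be no later than week 17.39 − 7 = 10.39 (nominal date) or 15.39 − 7 = 8.39 (window opening).

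**3. Sensitivity.** If the initial appointment in week 12 is not counted as a session, everything moves one week later. Courses of 6 or more then overlap the nominal date and courses of 4 or more overlap the window's opening. The eighth session falls in week 20, still 26.09 − 20 = 6.09 weeks before 6 months.

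**4. Sample size.** 26 × (1 − 0.25) = 19.5, which agrees with the stated 18 to 20 completers. The contradiction does not affect this figure.

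**The case against.** **The 4-month contact could be an additional or preparatory call.** Appendix 2, *When and how much*, describes it as a call to arrange the repeat, which leaves room for the repeat itself to come later. This does not hold up. Section 12 has participants invited at that contact to repeat the questionnaires, Appendix 2 *How* names a 4-month follow-up for the outcome measures, and the schedule of events has no 4-month column.

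**This looks like left-over wording.** Six places against three, with the outcome definition and the schedule on the same side, suggest that 6 months is intended. That is probably right, and it makes the fix easy. It does not remove the risk, because one of the three is the nurses' instruction.

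Stronger readings are tempting, but the document does not support them.

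- *The 4-month date is incompatible with the therapy timetable.* It is not. Counting the first appointment as session 1, the longest permitted weekly course ends in week 19, inside the Section 12 window. Appendix 2 says R-TEP usually takes 2 to 4 sessions; on the same count, four weekly sessions from week 12 end in week 15, before the window opens. Appendix 2 *How* also places the follow-up after therapy is complete. Overlap is an edge case in one arm of 13, although Section 12 and *When and how much* count from discharge and so do not exclude it.
- *The 75% criterion cannot be scored.* It can be counted under either date. What it lacks is a unique due date.
- *The treatment effect would be diluted by a known amount, or follow-up would be split between dates.* The documents give no distribution of start weeks or session counts, so no dilution can be computed, and the effectiveness data are exploratory. In a single-centre trial one team may well settle on one date.
- *The 3-month reference is a third outcome date.* It is called a session and may be held face to face, whereas the outcome questionnaires go by post or telephone. It may be a therapist contact.

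**Conclusion.** The contradiction is real, and nothing in the protocol text resolves it. It is an internal inconsistency about when the only post-baseline assessment takes place, and the two dates are about 8.7 weeks apart. It should be corrected before follow-up, because an assessment taken at the wrong time cannot be retaken at the right one.

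The contradiction itself needs no assumption. The overlap with therapy is a lesser, conditional consequence. It rests on weekly sessions kept to schedule, a start at or near week 12, and the initial appointment counting as the first session. On those terms it affects courses of 7 or 8 sessions at the nominal 4-month date and 5 or more at the window's opening. No on-schedule weekly course overlaps at 6 months. The number of participants affected cannot be estimated from the document. The patient flow diagram (Figure 1) could not be read and is not counted on either side.

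**What to change.** - In Section 12, and in Appendix 2 under *How* and *When and how much*, change the assessment time to 6 months after hospital discharge, to match Section 8.6 and the schedule of events.
- State one window for it (for example ± 2 weeks) in Section 12 and in the schedule, and use that window when counting completion for the 75% criterion.
- In Appendix 2, *Tailoring*, say whether the 3-month follow-up session is a therapist contact or an outcome assessment, and reconcile it with the schedule, which shows no such session.
- Record the date of the last therapy session and the date of the outcome assessment for each participant, so that the interval between them can be reported.

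The cost is a wording amendment, new dates on the nurses' call list and two date fields on the case report form. No extra visits or participants are needed, and the sample size stands.

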**Post-traumatic stress disorder:**

The PTSD Checklist-Civilian Version (PCL-C) is a validated, standardised self-reporting questionairre for PTSD comprising of 17 items that correspond to key PTSD symptoms[77]. Using a 5-point scale, participants are asked to indicate how much they have been bothered by these problems within the last month. (1= not at all; 5 = Extremely) PCL-C is rated by adding total scores.

**Anxiety and depression:** Hospital Anxiety and Depression Scale (HADS) is a 14-item, self-reported measure with 7-items relating to symptoms of anxiety and 7-items relating to depression[78]. Each item is scored from 0-3, providing categorical total scores for anxiety and depression. 0-7 = normal. 8-10 = borderline. 11-21 = abnormal.

**Cognitive function:** Montreal Cognitive Assessment (MoCA) is a validated tool, used to detect cogntive impairment[79]. MoCA is a 30-point test of short-term memory, visuospatial ability, executive function, attention, language, abstract reasoning and orientation. Scores range from 0-30. A score higher than 26 is considered to indicate normal cognitive function.

**Health Related Quality of Life:** EQ5D -5L comprises five quality-of-life dimensions; mobility, self-care, usual activities, pain/discomfort andanxiety/depression. Participants report levels ranging from ‘no problems’ to ‘extreme problems’.

**Resilience:** The Brief Resilience Scale is a validated measure of resilience. The capacity to recover from a traumatic event is dependent on mental processing of those trauma.

**Physical activity:** Patients will wear a wristband activity monitor following consent and at final assessment point, 6-months post-hospital discharge. The equipment has been validated for medical use and will be worn 24 hours per day for 7 consecutive days.

**Nutritional assessment:** The scored Council of Nutrition Appetite Questionnaire provides a validated assessment of appetite and predicted weight-loss and takes approximately 5-minutes to complete.

- 1. ***Additional data***

Hospital research staff will provide the following demographic and hospital admission information:

Age

Gender

Living arrangements

Postcode

Ethnicity

Employment status

Pre admission functional comorbidity index

ICU diagnosis

APACHE II score [81]

Duration of level 3 care

Duration of level 2 care

ICU and hospital length of stay

Days of ventilation

Sedation days

Episodes of delirium according to daily CAM-ICU measures[82]

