The recent traumatic episode protocol (R-TEP) is a version of EMDR, developed to help with the processing of traumatic events before the psychological damage becomes entrenched. Using EMDR R-TEP, an individual’s psychological trauma is addressed in a matter of a few therapy sessions, thus targeting the trauma in its very early stages. There is emerging evidence that EMDR R-TEP may be applicable to trauma treatment in survivors of critical care. A pilot study carried out in France used EMDR R-TEP sessions in emergency room patients, which led to significant reduction in PTSD symptoms compared to a 15-minute reassurance and control groups.

Social distancing guidelines and the potentially long-term nature of the Covid-19 epidemic require the adoption and robust testing of technological solutions, in order to assure access to best possible psychological care.

With a clear need to address post-critical care psychological complications, and emerging evidence of EMDR R-TEP’s effectiveness in reducing trauma levels in related populations, there is a compelling case to understand whether an online EMDR R-TEP intervention may be effective in reducing psychological complications in survivors of Covid-19 related critical illness in the UK.

1. **What (materials)**: The online EMDR R-TEP intervention requires the use of a R-TEP worksheet. The clinician and participant would progress through the worksheet in a gradual manner, following the 8-phase approach of the R-TEP. The worksheet is a crucial part of the intervention as the participant would often have to refer to it throughout the treatment process.

In addition, the following hard copy outcome measures will be used in the study:

- PTSD Checklist-Civilian Version (PCL-C)
- Hospital Anxiety and Depression Scale (HADS)
- Montreal Cognitive Assessment (MOCA)
- Health Questionnaire (EQ-5D-5L)
- World health Organisation Disability Assessment Schedule (WHODAS 2.0)
- Patient Generated Subjective Global Assessment Nutritional status (PG-SGA)
- Brief Resilience Scale (BRS)
- Wrist worn activity monitoring
- Subjective Units of Distress (SUDs)

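### The MoCA is placed among the assessments repeated by post or telephone, and neither route as written yields the 30-point score that the protocol describes

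*Protocol*

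**What the plan says.** Cognitive function is the third secondary objective in the Aims, and the MoCA is its measure. Under Secondary outcome measures the protocol states that "All secondary outcome measures will be collected at baseline and 6-months post-hospital discharge", and the schedule of events marks the MoCA at both points. The same section describes the instrument: "MoCA is a 30-point test of short-term memory, visuospatial ability, executive function, attention, language, abstract reasoning and orientation". It adds: "A score higher than 26 is considered to indicate normal cognitive function".

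Section 12 (Data collection and confidentiality) says how follow-up is done. Research nurses telephone the participant, and then "Participants will be invited to repeat the baseline questionnaires, which will be posted to them with a pre-paid envelope". The alternative is a call: "If participants prefer, the questionnaires can be completed over the telephone".

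Appendix 2 brings the MoCA into this procedure. Its materials item says that "the following hard copy outcome measures will be used in the study" and lists the MoCA among them. Its procedure item defines the baseline assessment by that list. Its item on timing and amount says that the nurses' call is to arrange a repeat of the baseline assessments, and ends: "Patients will be able to complete these assessment questionnaires by post or over the telephone".

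**The concern.** A self-report scale such as the HADS can be filled in at home or read out over the telephone. The MoCA, as this protocol describes it, is a performance test: the score depends on what the person can do when the items are put to them. The follow-up procedure is written for questionnaires, yet the protocol puts the MoCA through it.

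At stake is the interpretation of secondary objective 3. If the 6-month scores come from a mixture of unsupervised forms and calls, a difference between participants, or between a participant's two time points, may reflect how the test was given and not cognition. These data are also meant to inform the design of a later trial, so an unsuitable procedure could be carried forward.

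**Working it through.** This is mainly a comparison of texts.

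**Step 1: is the MoCA in the postal or telephone set?** Section 12 speaks of questionnaires, which alone would leave room for a separate arrangement. Appendix 2 removes most of that room:
- Materials: the MoCA is on the list of outcome measures.
- Procedure: baseline is carried out with that list.
- How: after therapy, participants are contacted by post to complete the repeat outcome measures.
- When and how much: the baseline assessments are repeated by post or telephone.

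Read in sequence, these lines include the MoCA. No other passage gives it a visit, a video administration, a remote version or adjusted scoring.

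**Step 2: does either route deliver the test described?**

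| Feature in the protocol's description | Posted form | Telephone call alone |
|---|---|---|
| Short-term memory | Nobody present to control how the items are attempted | Can be asked, but conditions are unseen |
| Visuospatial ability | Items can be seen, but work is unsupervised | Items cannot be presented or watched |
| 30-point total, threshold 26 | Total obtainable, conditions not secured | Full total not obtainable by the call itself |

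**Step 3: what would lost points do to the threshold?** The protocol gives no points per domain, so let v be the number of points that cannot be tested by telephone (an assumption). The maximum is then 30 − v.
- v = 1, 2, 3: maximum 29, 28, 27. A score above 26 is still possible.
- v = 4 or more: maximum 26 or less. Nobody could be classed as normal.

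The threshold may therefore survive or fail, and the documents do not say which.

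**Step 4: is the mode the same across time and arms?** Section 12 says only that baseline data are collected after consent. Recruitment may take place in hospital, or by telephone after discharge, so baseline could be face to face or remote. At follow-up the participant chooses, after randomisation. Nothing in the text makes the mode equal within a participant or between arms.

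**Step 5: how many scores?** Section 9 gives 26 recruited and 25% mortality or loss: 26 × (1 − 0.25) = 19.5, which agrees with its stated 18 to 20 completers. All of their follow-up MoCA scores would come through this procedure.

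**The case against.** The strongest reply is that the mode is unspecified and has not been shown to be invalid. Section 12 refers to questionnaires, while the protocol elsewhere calls the MoCA a test. The 7-day activity monitor is also due at 6 months and can be neither a form nor a call, so section 12 cannot describe the whole battery. This has some force for section 12. It does not remove the Appendix 2 sequence, which speaks of outcome measures and baseline assessments and has the MoCA on its list.

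Appendix 2 also names other follow-up modes: Skype or Zoom under Where, and a 3-month session face to face or by telephone under Tailoring. The first concerns therapy sessions, which controls do not have. The second matches no point in the schedule. Neither mentions the MoCA. They are conflicts to reconcile and do not supply a route for it.

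Three stronger readings are tempting but unsupported:
- *No valid score can be obtained, and every telephone score has a maximum below 30.* A nurse could put verbal items by telephone while the participant works on the posted form. The protocol does not describe this, but does not exclude it. The supportable claim is limited to the two routes as written.
- *Follow-up cannot be compared with baseline.* Baseline mode is not stated and may be remote for those consented after discharge. Mixed modes are a risk and have not been shown to occur. If both arms happened to use one mode, the between-arm comparison would suffer less than change from baseline.
- *The 75% completion criterion will be missed because of the MoCA.* The margin is thin: 75% of 26 is 19.5, so 20 are needed, and 18, 19 or 20 completers are 69.2%, 73.1% or 76.9%. But the Primary Outcome measure section does not say that every instrument must be complete, so a link to the MoCA is not established.

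It is also fair that the MoCA is one of several exploratory measures in a feasibility study and that no decision criterion uses its score.

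**Conclusion.** The point holds in a limited form. The only routes that the protocol gives for repeating the baseline assessments, the MoCA among them, are post and telephone. Neither, as written, produces the 30-point score with memory and visuospatial items that the protocol describes and reads against 26. This is an unsuitable stated procedure and more than a missing detail.

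It touches all planned follow-up MoCA scores (18 to 20) and one secondary objective. The feasibility conclusions are not shown to be affected. The size of any bias cannot be calculated, because the documents give neither points per domain, nor the baseline mode, nor the expected split between post and telephone.

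The conclusion rests on reading the Appendix 2 items together, and on the judgement that a memory test needs someone present and that visuospatial items must be seen. Section 12 and parts of Appendix 2 place the follow-up contact at 4 months, against 6 months elsewhere. That is a separate contradiction, and this point does not depend on how it is settled.

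**What to change.** In section 12 and Appendix 2:
- Take the MoCA out of the set of questionnaires repeated by post or telephone.
- State that a research nurse administers it live by video call at follow-up, in both arms. The Skype or Zoom provision in section 12 is written for the therapy team, so extend it explicitly to the research nurses and to control participants.
- Name the version, use the same mode and version at baseline where possible, and record the mode at each time point.
- Where video is impossible, report any reduced, non-visual score separately and do not read it against 26.
- Reconcile the other follow-up modes mentioned in Appendix 2 with this arrangement.

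The cost is a short video call for about 20 participants at follow-up, made by nurses who already telephone them, plus a call at baseline for those seen remotely. A few participants without video access will have no full score.
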